## 7.9. Studies

The study includes three sub-studies:

# Practices and challenges in the laboratory diagnosis of cryptococcosis in six hospitals in the three southern provinces of Mozambique.

This is a cross-sectional study with a mixed approach. The qualitative approach will be generic, where the current situation will be assessed before the intervention is implemented (Figure 2: Pre-implementation phase) in order to identify elements of the social, health, administrative, and structural context that may or may not favor the intervention in the local context.

The assessment of the current situation will be carried out in six hospitals (MCH, MGH, JMGH, MPH, XPH, and CHC) over three months. Sampling will be non-probabilistic, and intentional with regard to the participants and by convenience with regard to the study sites.

The data for this study will be obtained through semi-structured questionnaires (Annexes I, II, and IV) and interviews (Annex III) with health professionals from each hospital (clinicians from the medical service and microbiology laboratory technicians); and a list will be made of the equipment, existing material and a description of the cryptococcosis diagnoses currently carried out in each hospital involved in the study and to identify barriers and facilitators to implementing the technique of diagnosing cryptococcosis with urine samples.

The data will be analyzed using the R studio statistical package, where the following analyses will be carried out: descriptive analysis (calculating frequencies, mean or median, standard deviation, and variance); and chi-square to compare frequencies. The results will be described and presented in tables and graphs. A p-value of <0.05 will be considered significant.

# To implement the technique of laboratory diagnosis of cryptococcosis using the China ink method in urine as a point of care in selected hospitals in three southern provinces of Mozambique.

This is a stepped wedge trial. Sampling will be non-probabilistic by convenience in relation to the study sites and purposive in relation to the participants.

The study will be carried out in six hospitals (MCH, MGH, JMGH, MPH, XPH, and CHC) over six months. The Adaptation Phase will be the beginning of the iteration with the new test, the healthcare professionals (clinicians in medical service and laboratory technicians assigned to the microbiology sector) adapt to the workflow associated with the intervention (Figure 2). During the three months of adaptation, the researcher will carry out training on the care, diagnosis and treatment of cryptococcosis using urine dye (5 to 20 ml of the sample) with intentionally selected healthcare professionals, the diagnostic guide tools will be provided and an information-sharing workflow will be established between the laboratory and the clinicians.

It's up to the clinician to decide which patients to ask for a urine sample to diagnose cryptococcosis and also to decide what clinical information to share with the laboratory according to each situation. We will provide the national health system with a resource for the diagnosis of cryptococcosis, instead of empirical treatment when routine treatment is not available. Therefore, the clinician is free to request routine or experimental testing. If the clinician decides to request a urine sample for the diagnosis of cryptococcosis, the laboratory will provide feedback according to the clinician's request in order to follow up on the patient.

The implementation of the diagnosis of cryptococcosis with Chinese ink using non-invasive urine samples at the selected sites will take place over 6 months. In this implementation phase, the health professionals assigned to the medical service with knowledge of the intervention (new test for cryptococcosis) will request that it be carried out by colleagues from the laboratory who have been previously trained in its execution. Throughout this phase (Figure 2) monitoring of clinicians' behaviour in relation to the use of the new diagnostic will take place and documentation of its implementation will be captured (Appendix V).

The data will be analysed using the R studio statistical package. The frequencies of the variables (number of tests requested with and without feedback, number of trained professionals) will be calculated and the frequencies will be compared using the Chi-square test.

The correlation between (number of professionals trained and number of tests requested) will be determined; the Odds Ratio (OR) will be estimated using regression: services covered/improved (dependent variable) and independent variables: professional trained, years of practice, level of education of the professional; age, gender.

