**Tabela 1. Desenho de estudo *Stepped-wedge***

| Phases | Months/2024-2025 | | | | | | | | | | | | | | |
| --- | --- | --- | --- | --- | --- | --- | --- | --- | --- | --- | --- | --- | --- | --- | --- |
|  | 1 | 2 | 3 | 4 | 5 | 6 | 7 | 8 | 9 | 10 | 11 | 12 | 1 | 2 | 3 |
| MCH | C | C | C | C | PI | AD | I | FU | FU | FU | FU | FU | FU | FU | FU |
| MGH | C | C | C | C | PI | AD |  | I | FU | FU | FU | FU | FU | FU | FU |
| JMGH | C | C | C | C | C | PI | AD |  | I | FU | FU | FU | FU | FU | FU |
| MPH | C | C | C | C | C | PI | AD |  |  | I | FU | FU | FU | FU | FU |
| XPH | C | C | C | C | C | C | PI | AD |  |  | I | FU | FU | FU | FU |
| CHC | C | C | C | C | C | C | PI | AD |  |  |  | I | FU | FU | FU |

**C-** Control**; PI**-Pré-implementation; **AD**- Adaptation; **I**-Implementation; **FU**- follow-up

The mixed method approach will allow triangulation and complementarity of the findings, giving the possibility of strengthening the research conclusions (33). The quantitative part will be cross-sectional and the qualitative part will be generic. Quantitative data such as (the number of tests carried out with Chinese ink, positive results, negative results, response time, level of academic education of health professionals, number of health professionals allocated to HIV services, number of trained professionals, percentage of services that adhered to the intervention, number of microscopes in existence) will be obtained through a questionnaire administered to health professionals and by observation based on the previously drawn up script.

In the qualitative part, through semi-structured interviews, topics will be explored that address (challenges for: diagnosis, and treatment of cryptococcosis, and the satisfaction of health professionals in relation to the intervention will also be evaluated).

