**Quantitative data analysis**

Quantitative data will be analyzed using the R studio statistical package. Univariate descriptive analyses will be carried out (mean or median age, standard deviation and variance will be calculated), percentage frequencies of the following variables: tests requested, doctors/laboratory technicians who adhered to the intervention, chi-square to check for associations between the intervention/test and the variables (level of education of the professional, availability of the test, severity of the disease and gender) and logistic regression to estimate the relationship between adherence to the test and factors severity of the disease, work overload in the US/laboratory, level of education of the professional, shift, gender, availability of laboratory services.

A Likert scale will be used to assess the level of satisfaction of all those involved in the intervention (doctors and laboratory technicians) during the study period. And the frequencies of the information obtained will be calculated.

The results will be described and presented in tables and graphs using the Microsoft Excel program. A p-value of <0.05 will be considered significant.

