# Evaluation of the RE-AIM-based implementation of the technique of laboratory diagnosis of cryptococcosis using the China ink method in urine as a point of care in southern Mozambique

This is a cross-sectional quantitative study aimed at measuring the contribution of the diagnosis introduced (intervention effect) in the six hospitals (MCH, MGH, JMGH, MPH, XPH and CHC) over three months. Sampling will be non-probabilistic, intentional with regard to the participants (healthcare professionals) and by convenience concerning the study sites.

In the Implementation Evaluation Phase (Post-implementation), during three months the implementation will be evaluated using the RE-AIM conceptual framework with five domains reach (comprehensiveness), effectiveness, adoption (acceptability and representativeness), implementation and maintenance (sustainability) of the intervention in the hospitals. Data collection will be based on previously prepared questionnaires and standardized scripts coupled to the REDCap platform loaded onto the tablet.

- Reach will be calculated through the proportion of individuals covered by the intervention (clinicians and laboratory technicians).
- Efficacy will be assessed by checking laboratory and clinical results, time to diagnosis and satisfaction of health professionals.

The study includes an evaluation at the beginning (baseline) pre-implementation and at the end post-implementation, where laboratory and clinical results, time to diagnosis and satisfaction of health professionals will be verified at both times. The efficacy of the intervention will therefore be evaluated before and after implementation. WHO recommendations will be consulted, which recommend screening and treatment to prevent complications from a cryptococcal infection. The test to be implemented will contribute to starting treatment on the same day as the consultation and based on the aetiological diagnosis.

- Adoption will be explored through the representativeness of the services that have adopted the implementation including sample flow, laboratory processing and feedback, use of scripts drawn up and made available during the intervention.
- A Likert scale will also be used to analyze the satisfaction of all health professionals covered by the intervention during the study period (clinicians and laboratory technicians).

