| To evaluate the implementation of the India ink method as a point of care laboratory diagnosis in selected hospitals, based on the RE-AIM conceptual framework. | Number of services and number of providers that adhered to implementation, age, sex, number of samples tested, test availability, initiation of treatment after positive test. | Frequency (professionals who adhered to the intervention, samples tested, services that adhered to the intervention, age and sex. Chi-square compare frequencies Ex: (relationship between characteristics of professionals and the type of test requested);  Multivariate regression to estimate the “Odds Ratio” (OR) of the relationship between adherence to testing (PS) and the variables: severity of the disease, age of the professional, sex, US, availability of services in the laboratory, and feedback |

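### The measures tied to the stepped-wedge sub-study have no control-period value, and the outcomes planned for both periods are not measured alike, so the control months give little basis for an intervention effect

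*Protocol*

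**What the plan says.** Under section 7.9, sub-study 2 states: "This is a stepped wedge trial". For its implementation phase, "monitoring of clinicians' behaviour in relation to the use of the new diagnostic will take place and documentation of its implementation will be captured", with Annex V named as the tool for documenting implementation. The same sub-study leaves the clinician free to choose between the routine test and the new one.

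Several measures concern the new test only:

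- The quantitative analysis section plans "logistic regression to estimate the relationship between adherence to the test and factors severity of the disease" and other factors.
- The variables table lists use of the supplied scripts for the second objective and "Number of services and number of providers that adhered to implementation" for the third.
- Annex V asks for satisfaction with India ink in urine.

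Other measures exist with or without the new test. The variables table lists type of tests requested and number of samples tested for the first and second objectives, and response time for the second. Sub-study 3 describes its aim as "measuring the contribution of the diagnosis introduced (intervention effect" in the six hospitals. It says that laboratory and clinical results, time to diagnosis and staff satisfaction will be checked at baseline and again after implementation.

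Table 1 in section 7.1 sets out 15 months for each hospital. The first hospital's row begins "MCH | C | C | C | C | PI | AD | I" and the last hospital's row begins "CHC | C | C | C | C | C | C | PI | AD".

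**The concern.** A stepped wedge estimates an effect by comparing one outcome, scored in the same way, in unexposed and exposed cluster-periods. A measure that is defined only once the test is on offer has nothing to be compared with, however many control months the design contains.

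Uptake also answers a different question from the one the protocol raises. The Contribution section hopes for more laboratory confirmation among suspected cases. If clinicians send urine in place of a sample they would have sent anyway, uptake is high while the number of people tested or confirmed does not change. Only counts across all methods can show which of the two happened.

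**Working it through.** **1. Table 1 cells.** Inputs: the six rows of Table 1, 6 hospitals × 15 months = 90 cells.

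| Hospital | C | PI | AD | Uncoded | I | FU | Sum |
|---|---|---|---|---|---|---|---|
| MCH | 4 | 1 | 1 | 0 | 1 | 8 | 15 |
| MGH | 4 | 1 | 1 | 1 | 1 | 7 | 15 |
| JMGH | 5 | 1 | 1 | 1 | 1 | 6 | 15 |
| MPH | 5 | 1 | 1 | 2 | 1 | 5 | 15 |
| XPH | 6 | 1 | 1 | 2 | 1 | 4 | 15 |
| CHC | 6 | 1 | 1 | 3 | 1 | 3 | 15 |
| Total | 30 | 6 | 6 | 9 | 6 | 33 | 90 |

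- Control: 30/90 = 33%.
- Control plus pre-implementation, clearly before the test: 36/90 = 40%.
- Implementation plus follow-up: 6 + 33 = 39, 39/90 = 43%.
- Status not settled by the text (adaptation and uncoded): 6 + 9 = 15, 15/90 = 17%.

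**2. What the new-test measures can be in the 36 earlier cells.** The number of urine tests is zero by construction. Adherence to the test, use of the scripts and satisfaction with the test are undefined, which is not the same as zero. In neither case is there a control value to compare with.

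**3. What uptake can say about added testing.** In one hospital-month let U be the adults tested with urine India ink. Split them as U = a + s + b, where a would otherwise have gone untested, s had urine in place of a routine test, and b had both. With demand otherwise unchanged, the change in adults tested is a. Knowing U gives only 0 ≤ a ≤ U. At the extreme of complete substitution, urine goes from 0 to 100% of tests while a = 0. This is the limit of the range and not a forecast; the protocol has no figure that would place a within it.

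**4. Outcomes planned at both times, set against the annexed forms.**

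| Outcome | Baseline forms | After implementation (Annex V) |
|---|---|---|
| Number tested | Annex II: staff estimate of samples per week, in bands; Annex IV: how often the clinician requests the test | Agreement that more people with HIV could be tested; banded guess at the share of patients who benefited |
| Laboratory positives | Annex II: banded frequency among suspect samples | No item |
| Response time | Annexes II and IV: best estimate in minutes or hours | Satisfaction with response time |
| Treatment after a positive | Annex IV: best estimate of time to start | Agreement that treatment improved (clinician form) |
| Deaths, admissions | No item | Agreement that deaths fell; clinician form also on admissions |
| Satisfaction | No scale in Annexes I, II or IV | Five-point scales |

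No row has the same measurement in both columns. The list of quantitative data in section 7.1 counts tests done with the ink without separating urine from cerebrospinal fluid.

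**5. Timing.** The last control cell is in month 6 (XPH, CHC) and the first implementation cell in month 7 (MCH), so no control cell shares a month with an implementation or follow-up cell. The only cells before a start in months when another hospital has started are 2 PI + 4 AD + 9 uncoded = 15, in months 7 to 11 (5 + 4 + 3 + 2 + 1 = 15). How these are classified therefore decides whether there is any concurrent comparison.

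**The case against.** The strongest reply is that the protocol already separates effect from uptake. Sub-study 3 assigns laboratory and clinical results, time to diagnosis and satisfaction to efficacy, at both times, and treats coverage, adoption and fidelity as separate domains. Tests and samples appear in the variables table for the situation analysis as well as for implementation. Monthly tabulation could be left to an analysis plan, and the observation guide mentioned in section 7.8, which is not shown, might collect counts.

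Much of this stands, and it rules out three stronger readings:

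- A reader might infer that all the stepped-wedge outcomes are impossible in control months. They are not: tests by any method, samples, response time and laboratory results all exist there.
- A reader might infer that any uptake will be declared an effect. No section compares uptake with control months; adherence is regressed on staff and service factors, and requests are correlated with numbers trained. Nor would any uptake be significant. In a naive comparison of 0/30 control cells with x/39 exposed cells, ignoring clustering and time, x = 1 gives Fisher p = 1.00, and p < 0.05 needs x = 6 (p = 0.032), or x = 5 by uncorrected chi-square (p = 0.042).
- A reader might count 30 + 6 + 6 + 9 = 51 of 90 months as free of the urine test. That is only an upper limit, because contact with the new test begins in the adaptation phase and the uncoded months have no stated status.

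What the reply does not answer is measurement. Sub-study 3 promises two time points rather than a series across the wedge, and the annexed forms cannot deliver even those two on one scale. An analysis plan cannot recover control-month counts that were never collected.

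**Conclusion.** The point holds in this limited form. For use of the urine test, adherence, script use and satisfaction with the new test, 30 control hospital-months (36 with pre-implementation, 40% of the table) give no comparison. Uptake leaves the number of additional adults tested anywhere between none and all of those given the urine test. Outcomes that could carry the comparison are named, but no primary one is chosen, and the annexed forms record them as staff estimates before and opinions after.

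This rests on the annexes being the instruments for these outcomes, on the unseen observation guide not already holding monthly counts, and on Table 1 being read as printed. It should be corrected because the protocol sets out to measure an intervention effect. It does not touch the descriptive implementation findings, which remain useful.

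**What to change.** 1. Base the intervention effect on two outcomes measured identically in every month: adults tested for cryptococcosis by any method, and adults laboratory-positive by any method, per hospital-month. Take both as counts from the laboratory registers for all 15 months, control months included. Count people rather than tests, so that a patient given both tests is not counted twice.
2. State how pre-implementation, adaptation and uncoded months are classified.
3. Report urine-test uptake, adherence and satisfaction with the new test as descriptive measures after each hospital's start. Show urine tests also as a share of all cryptococcosis tests, so that substitution is visible.
4. If time to diagnosis or satisfaction is to be compared before and after, put the same item on the baseline and the later form.

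The cost is abstraction of monthly totals by the researcher who already visits each site. Register quality may differ between hospitals; Annex II already asks whether a register exists. Because no control cell is concurrent with an implementation or follow-up cell, better outcomes do not by themselves remove confounding with calendar time, and the report should say so.

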# Evaluation of the RE-AIM-based implementation of the technique of laboratory diagnosis of cryptococcosis using the China ink method in urine as a point of care in southern Mozambique

This is a cross-sectional quantitative study aimed at measuring the contribution of the diagnosis introduced (intervention effect) in the six hospitals (MCH, MGH, JMGH, MPH, XPH and CHC) over three months. Sampling will be non-probabilistic, intentional with regard to the participants (healthcare professionals) and by convenience concerning the study sites.

In the Implementation Evaluation Phase (Post-implementation), during three months the implementation will be evaluated using the RE-AIM conceptual framework with five domains reach (comprehensiveness), effectiveness, adoption (acceptability and representativeness), implementation and maintenance (sustainability) of the intervention in the hospitals. Data collection will be based on previously prepared questionnaires and standardized scripts coupled to the REDCap platform loaded onto the tablet.

- Reach will be calculated through the proportion of individuals covered by the intervention (clinicians and laboratory technicians).
- Efficacy will be assessed by checking laboratory and clinical results, time to diagnosis and satisfaction of health professionals.

The study includes an evaluation at the beginning (baseline) pre-implementation and at the end post-implementation, where laboratory and clinical results, time to diagnosis and satisfaction of health professionals will be verified at both times. The efficacy of the intervention will therefore be evaluated before and after implementation. WHO recommendations will be consulted, which recommend screening and treatment to prevent complications from a cryptococcal infection. The test to be implemented will contribute to starting treatment on the same day as the consultation and based on the aetiological diagnosis.

- Adoption will be explored through the representativeness of the services that have adopted the implementation including sample flow, laboratory processing and feedback, use of scripts drawn up and made available during the intervention.
- A Likert scale will also be used to analyze the satisfaction of all health professionals covered by the intervention during the study period (clinicians and laboratory technicians).
- During implementation, the fidelity of health professionals in relation to the diagnosis, care and treatment of cryptococcosis based on documented observation will be assessed.
- Maintenance (sustainability) will be assessed based on the simplicity of the intervention (laboratory diagnostic technique for cryptococcosis using urine), the workflow and the cost of the test implemented.

The data obtained in this study will be entered into the R studio statistical package, where the following analyses will be performed: Descriptive analysis (calculate frequencies, mean and variance), Chi-square to compare frequencies and multivariate regression to estimate the “Odds Ratio” (OR).

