## Study timeline

- The study will last approximately 1 year and 3 months with different phases:
- First phase: Assessment of the current situation: (duration 3 months):
- Second phase: Adaptation (duration 3 months);
- Third phase: Implementation of the intervention in phases guided by the PAD (duration 6 months);
- Fourth phase: Evaluation, sustainability and results according to the RE-AIM (duration 3 months).

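### The RE-AIM evaluation is one end-of-study window for hospitals that start up to five months apart, so hospital differences in adoption and use are partly differences in time since start

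*Protocol*

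**What the plan says.** Section 7.3 (Study timeline) gives the total length: "The study will last approximately 1 year and 3 months with different phases". Of the four phases listed there, a situation assessment takes 3 months, training and adjustment of the workflow another 3, and the staggered roll-out 6. The closing one reads "Fourth phase: Evaluation, sustainability and results according to the RE-AIM (duration 3 months".

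The third sub-study in section 7.9 describes the evaluation as cross-sectional, carried out "in the six hospitals (MCH, MGH, JMGH, MPH, XPH and CHC) over three months". It places the work after implementation: "In the Implementation Evaluation Phase (Post-implementation), during three months the implementation will be evaluated using the RE-AIM conceptual framework". On timing it adds: "The study includes an evaluation at the beginning (baseline) pre-implementation and at the end post-implementation".

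Table 1 (section 7.1) marks one implementation month (I) per hospital: MCH in month 7, MGH 8, JMGH 9, MPH 10, XPH 11 and CHC 12. Every month after I is follow-up (FU), up to month 15. The table has no label for the evaluation.

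The analyses planned for this sub-study are frequencies, chi-square tests and a regression giving odds ratios. The covariates listed in the variables and data analysis plan include the health unit (US) but not time since start. The same sub-study bases maintenance on how simple the technique is, on the workflow and on the test's cost.

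**The concern.** A staggered roll-out followed by one common closing assessment gives each hospital a different length of experience when it is assessed. Several planned measures depend on that length:

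- The numbers of samples tested and of providers and services adhering can change with time in use. If counted from the start, they also grow with the number of months.
- Annex V asks whether the urine test has always been available since it was introduced. A hospital with more months behind it has had more time to run out of reagent.
- Annex V also asks whether deaths have fallen. The clinician form asks the same of admissions for complications. One to three months is a thinner basis for that judgement than six to eight.

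At stake is the third specific objective. A hospital that looks better or worse on adoption may simply be earlier or later in its own use of the test, and a sustainability statement covering all six hospitals would include one with very short experience.

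**Working it through.** **1. The plan's own duration.** The phases sum to 3 + 3 + 6 + 3 = 15 months. This equals the stated 1 year and 3 months (12 + 3 = 15) and the 15 month columns of Table 1. As the last phase, the evaluation then occupies months 13-15.

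**2. Time since start.** Time since start = evaluation month − month of the I cell.

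| Hospital | I month | FU months in Table 1 | Time since start, months 13-15 | FU months 1-3 fall in |
|---|---|---|---|---|
| MCH | 7 | 8 | 6-8 | 8-10 |
| MGH | 8 | 7 | 5-7 | 9-11 |
| JMGH | 9 | 6 | 4-6 | 10-12 |
| MPH | 10 | 5 | 3-5 | 11-13 |
| XPH | 11 | 4 | 2-4 | 12-14 |
| CHC | 12 | 3 | 1-3 | 13-15 |

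The gap between MCH and CHC is 12 − 7 = 5 months. It does not depend on where the common window is placed.

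**3. Sensitivity to the window.** Section 10 has a three-month column for 07-09/2025. Assume that the evaluation falls there and that month 1 is January 2024. The window is then months 19-21, giving MCH 12-14 and CHC 7-9 months. The gap is still 5 months.

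**4. Can adjustment repair it?** Take one survey of the 36 professionals listed in section 7.5 (10, 6, 6, 5, 5 and 4 in table order), dated to month 14. Six hospital indicators plus time since start give a design matrix with 7 columns but rank 6. Time since start is fixed once the hospital is known, so a model that contains hospital cannot also estimate it.

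**5. What timing alone could do (illustration).**
- Counts: with the same monthly rate everywhere, totals over the FU months differ by 8/3 = 2.67 between MCH and CHC.
- Monthly use: the documents give no rate of change, so assume use falls by a fraction d per month at every hospital alike. At month 14 use is (1 − d)^7 of its starting level at MCH and (1 − d)^2 at CHC.
  - d = 0: no difference.
  - d = 5%: 0.698 against 0.903, a ratio of 1.29.
  - d = 10%: 0.478 against 0.810, a ratio of 1.69.
  - Rising use through learning would act in the opposite direction.

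**The case against.** Several points on the other side are sound, and they limit the finding.

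- **The window is inferred.** Table 1 does not label the evaluation, and the shading of the section 10 timeline cannot be read in the available text. A reader might take 1-3 months at CHC as fixed by the protocol. It follows from the phase lengths and is not stated. The 5-month gap holds for any common window.
- **Start could mean adaptation.** Sub-study 2 treats adaptation, which includes training, as first contact with the test. Adaptation is month 6 at MCH and month 8 at CHC, a gap of 2 months. That clock suits items on the training tools or technician confidence. It does not suit use, availability or adherence, which follow the I month.
- **Maintenance.** A reader might infer that the maintenance result is confounded in the same way as adoption. The protocol's definition does not support that, because simplicity, workflow and cost are not quantities that fade with months of use. What remains is how short the experience at CHC is.
- **Other data exist.** A reader might infer that the end survey is the only measurement. Fidelity is assessed during implementation, and sub-study 2 plans monitoring and documentation throughout that phase.
- **Pooling.** Nothing says that results will be reported only as one figure across hospitals.
- **Moving the survey is a trade-off.** Surveying each hospital in its own FU months 1-3 would equalise exposure. It would also tie hospital to calendar time and lose the late reading at the hospitals that started early.

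The last point argues against rescheduling. None of them removes the unequal exposure in the end evaluation, and no planned analysis uses time since start.

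**Conclusion.** The point holds for adoption, adherence, test counts and the Annex V items that depend on length of use. In the common closing phase, hospitals differ in time since start by up to 5 months. If the window is months 13-15, the range runs from 1-3 months at CHC to 6-8 at MCH. No adjustment of that single survey can separate the two influences.

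The 5-month gap rests only on Table 1 and on the window being common to all hospitals. The month ranges also assume that the phases run back to back. The size of any distortion is unknown: the 5% and 10% monthly declines are assumptions, and with stable use there would be none in monthly rates.

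Maintenance is affected mainly through the short record. A statement covering all six hospitals can rest on no more than the three FU months that CHC has in Table 1. This should be corrected, but it does not call for a change of design.

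**What to change.** Keep the end evaluation and amend the protocol as follows:

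1. State the calendar months of the evaluation, and confirm that they are common to all six hospitals.
2. Record with their month the monitoring data and test counts already planned for implementation and follow-up. Report tests requested, samples tested and adherence per month, by months since each hospital's own I month.
3. Compare hospitals on these measures over FU months 1-3, which all six have in Table 1 (from months 8-10 at MCH to 13-15 at CHC).
4. Show Annex V results by hospital, with months since start beside each.
5. Limit any six-hospital maintenance statement to the common follow-up, 3 months per Table 1. Report longer maintenance only for hospitals that have it; those with 6 FU months or more are MCH (8), MGH (7) and JMGH (6).
6. State that comparisons aligned on time since start still differ in calendar time, for example in reagent supply or staffing.

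The cost is protocol wording, a month field on the counts and a little extra tabulation. No participants, visits or study months are added. The maintenance claim becomes narrower, and differences between hospitals still cannot be read as causal.
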